## Abstract

**Background:**

The main hypothesis of this study is that patients having regular conventional haemodialysis (HD) will have a smaller decline in cardiac systolic function by using cooler dialysate. Cooler dialysate may also be beneficial for brain function.

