### Primary study outcome

Change in resting LVEF by cardiac magnetic resonance (CMR) at 12 months compared to baseline between the intervention and control group.

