### Sample size estimation

The primary aim in this study is to detect a 5% difference in LVEF as measured by CMR between the control and intervention group after 12 months. Using a two sample t test and assuming a mean LVEF of 67% in the control arm and equal Standard Deviation in each group of 6% [27], a study of 64 participants (32 per group) would permit the detection of a 5% difference in LVEF from baseline to 12 months between the intervention and control groups, with 90% power at 5%, 2-sided significance level. Allowing for study attrition and death of 10%, we aim to recruit 72 participants to achieve an evaluable sample of 64 participants.

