### Statistical methods

All the continuous variables will be tested for normality using their histograms and normality tests. The primary endpoint will be compared between the two groups at specific time points using the Mann U Whitney or Independent T-test. Repeated measures analysis will be used for testing the difference on primary endpoint between tests across the whole period. Poisson regression analysis will be used for comparing the frequency of intra-dialytic RWMAs between the two groups. Haemodynamic variables and other secondary endpoints will be analysed using repeated measures and Bonferroni’s test for multiple comparisons. Paired tests, Wilcoxon Signed test or Paired T-test, will be used for comparing the primary and secondary endpoints between two time points within each group. An alpha error at 0.05 will be judged as significant. Analysis will be performed using SPSS for Windows, v16 or Stata v10. Statistical analysis will be based on an intention-to-treat principle with all data analysed according to the patient’s original study group allocation regardless of death, crossover or early withdrawal.

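### Before-and-after significance tests within each arm are planned at the same 0.05 threshold as the between-arm test, with no stated role, and can suggest an effect of cooling where there is none

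*Protocol article*

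**What the plan says.** The main hypothesis in the Abstract is comparative: haemodialysis patients "will have a smaller decline in cardiac systolic function by using cooler dialysate". The Primary study outcome section agrees: "Change in resting LVEF by cardiac magnetic resonance (CMR) at 12 months compared to baseline between the intervention and control group". The Sample size estimation section sizes the trial on the same contrast, with the aim "to detect a 5% difference in LVEF as measured by CMR between the control and intervention group after 12 months".

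The Statistical methods section then lists three kinds of analysis for the primary endpoint:

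- a between-group test: "The primary endpoint will be compared between the two groups at specific time points using the Mann U Whitney or Independent T-test"
- a repeated-measures analysis: "Repeated measures analysis will be used for testing the difference on primary endpoint between tests across the whole period"
- tests within each arm, either Wilcoxon signed-rank or paired t, which also cover the secondary endpoints: "Paired T-test, will be used for comparing the primary and secondary endpoints between two time points within each group"

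One threshold follows for everything: "An alpha error at 0.05 will be judged as significant". The section does not call the within-arm tests descriptive. It does not say what may be concluded from them, or which result governs if they and the between-group test disagree.

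**The concern.** A smaller decline is a statement about the difference between two changes. Testing each arm's change against zero does not test that difference. The before-and-after change in one arm combines any effect of treatment with time on dialysis, regression to the mean, and the selection of patients who return for a second scan. Only the comparison of randomised arms separates these.

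The risk is a familiar misreading: control fell significantly, cooled did not, therefore cooling protects. Two arms with the same true decline can easily fall on opposite sides of 0.05 by chance. The wording makes the misreading easier. The between-group test is described at time points and not explicitly on change, and the repeated-measures sentence names no group-by-time contrast. The within-arm sentence is thus the only one in the section that plainly names a comparison of two time points. At stake is a claim of benefit that the randomised comparison would not support.

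**Working it through.** **Inputs from the article.** 32 evaluable patients per arm, two-sided 5% level, a 5-point LVEF difference, 90% power, and "equal Standard Deviation in each group of 6" points (Sample size estimation).

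**The plan's own figure first.** A two-sample t-test with difference 5 and SD 6 needs 31.25 per arm for 90% power, rounded up to 32. Power at 32 is 90.7%. Allowing 10% attrition, 64/0.9 = 71.1, so 72. The stated sample size reproduces.

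**Assumption.** The paired test needs the SD of the change, which the article does not give. If the SD is 6 at each visit and the baseline-to-12-month correlation is ρ, the SD of change is 6 × √(2(1 − ρ)). At ρ = 0.5 this equals 6, which is the working value. SDs of 4 and 8 show the range; they correspond to ρ = 1 − 16/72 = 0.78 and ρ = 1 − 64/72 = 0.11. The common decline in LVEF by CMR is not given either, so it is varied from 0 to 5 points.

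**Method.** Suppose both arms truly fall by the same amount d. For one arm, the paired t-test has noncentrality (d/SD) × √32; for d = 2 and SD 6 this is 0.333 × 5.657 = 1.886. Let p be the probability that one arm is significant in either direction, and u the probability that it shows a significant decline. The arms are independent, so:

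- P(significant decline in control, non-significant in cooled) = u(1 − p)
- P(exactly one arm significant, either way round) = 2p(1 − p)

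**Results, 32 per arm, SD of change 6, no true arm difference**

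| Shared decline (points) | p | Control declines, cooled not significant | Exactly one arm significant |
|---|---|---|---|
| 0 | 0.050 | 2.4% | 9.5% |
| 1 | 0.150 | 12.6% | 25% |
| 2 | 0.447 | 24.7% | 49% |
| 3 | 0.782 | 17.0% | 34% |
| 4 | 0.955 | 4.3% | 8.7% |
| 5 | 0.995 | 0.5% | 0.9% |

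Example at 2 points: u is practically equal to p, so 0.447 × 0.553 = 0.247.

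**Control-only split for other SDs of change**

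| Shared decline (points) | SD 4 | SD 8 |
|---|---|---|
| 0 | 2.4% | 2.4% |
| 1 | 20.1% | 9.1% |
| 1.5 | 24.9% | 14.5% |
| 2 | 17.0% | 20.1% |
| 3 | 1.6% | 24.9% |
| 4 | 0.0% | 17.0% |
| 5 | 0.0% | 6.6% |

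The peak is about 25% whatever the SD, because p(1 − p) is largest at p = 0.5, where it equals 0.25. The SD only moves the decline at which the peak occurs: about 1.5, 2.1 and 3 points for SD 4, 6 and 8.

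**Simulation check.** In 200,000 simulated trials per setting (SD of change 6), the control-only split came out at 12.8%, 25.0% and 17.0% for shared declines of 1, 2.1 and 3 points, in line with the formula. The between-arm t-test of change rejected in 4.9% to 5.1% of trials; by symmetry about 2.5% favour cooling. Across declines of 0, 1, 2.1 and 3 points, 68% to 91% of split results (either way round) came with a non-significant between-arm test.

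**The case against.** The strongest reply is that the article defines, sizes and plans a between-group comparison, and that the paired tests come later in the section as additions. This stands. A reader might infer that the plan gives up the randomised comparison, or ranks the within-arm tests equal to it. The documents do not support that: neither the outcome definition nor the sample size rests on the paired tests, and nowhere does the article say that efficacy will be judged from them. What they share with the between-group test is the threshold.

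Second, the risk depends on the true common decline. It is negligible at zero and at large declines. The only 12-month fall the article cites is 13%, by echocardiography, in patients with stress-induced wall motion abnormalities; if a fall that large were shared, both arms would be significant and a split would be very rare. This also stands as a limit. But that figure comes from a subgroup of prevalent patients and another imaging method, and the article gives no expected decline by CMR for incident patients. The hypothesis of a smaller decline also supposes some fall, so modest shared declines cannot be set aside.

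Third, cardiac images for the primary outcome are read blind to allocation, and Bonferroni's test is named for secondary endpoints. Both are useful, but neither makes a within-arm test a test of treatment. It would also be tempting to apply the percentages above to every endpoint. That is not supported, because the article gives no SD or expected change for any secondary endpoint; only the mechanism carries over.

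Fourth, an article condenses, and a full analysis plan might label these tests descriptive. But the article does not merely omit a detail here: it commits to the tests and states a threshold for significance. That wording can be judged as it stands.

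**Conclusion.** The point holds as a fault in a stated supporting analysis; the primary outcome itself is correctly defined. The within-arm tests cannot answer the trial's question, and they have no stated role beside the test that can.

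For LVEF with 32 per arm and no true arm difference, the misleading pattern in favour of cooling occurs in about 13% to 25% of trials when both arms fall by 1 to 3 points. It occurs in about 2.4% with no shared change, 4% at 4 points and 0.5% at 5 points. The between-arm test's error in that direction is 2.5%. These figures rest on an assumed SD of change of 6. The peak near 25% does not depend on that assumption, but the decline at which it occurs does. The change is worth making before analysis because it is nearly free.

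**What to change.** In the Statistical methods section, replace the within-group Wilcoxon signed-rank and paired t-tests with the mean change in each arm and its 95% CI, labelled descriptive and shown without p-values. Add that all efficacy conclusions rest on the between-group difference at 12 months adjusted for the baseline value, reported with its 95% CI.

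The baseline scan is already in the schedule, so no new data are needed. Dropping the within-arm tests costs no power: the between-arm test keeps 90.7% at 32 per arm under the plan's own inputs. The work is a change of wording and of analysis code, and the article describes the analysis as still to come.

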### Monitoring for adverse events

The number and proportion of participants who report treatment-emergent adverse events will be summarized for each treatment group. Treatment emergent events include events that start on or after allocation to the study assigned dialysate temperature.

### Trial completion

Commencing in September 2009, trial recruitment of 73 patients was completed by January 2012. Follow-up will be completed in January 2013 with results analysed and reported in mid-late 2013. Based on the final number recruited (73), the study has 90% power to detect a 5% difference in LVEF.

## Discussion

This study has been designed to provide evidence to help nephrologists determine the optimal dialysate temperature for preserving cardiac function in HD patients. The cooling protocol has been refined to optimise tolerability as informed by a significant body of preparatory studies to directly impact on HD-induced circulatory stress. Since the study was conceived we have expanded the list of vascular beds potentially vulnerable to this insult to include the kidney, gut and brain [39,40]. This study incorporates the ability to explore the hypothesis that cooler dialysate may be beneficial for brain microstructure and cognitive function.

One of the weaknesses of previous studies in HD patients has been the use of prevalent patients well established on dialysis. This brings a significant ‘survivor bias’ effect, as well as the loss of patients with a less severe risk phenotype over time to transplantation. Although it has made recruitment to this study more challenging we elected to restrict recruitment to patients within 180 days of dialysis initiation.

This study is predicated on measures of cardiac structure and function which are validated surrogate outcomes of relevant patient outcomes. The study design includes a variety of explanatory outcomes which may generate insights into mechanisms of any reported benefits and multi-organ effects of HD treatment. It is conceived that this study may provide the justification and sample size estimation required for a larger study predicated on cardiovascular events and mortality. The plausibility of this approach has been strengthened by recently published observations of reduced cardiovascular mortality in patients dialysed against cooled dialysate [41].

## Conclusion

Dialysate cooling is a well-tolerated, low-cost and universally available intervention. We hope that this pragmatic trial of cooling will provide important data informing the optimal therapy for HD patients. Although some consequences of HD induced circulatory stress might be addressed by extended treatment schedules, thrice weekly, in-centre HD is likely to remain the norm for the majority of HD patients for the foreseeable future. Therefore there remains a need for therapy refinement within that paradigm.

## Abbreviations

LVEF, Left ventricular ejection fraction; CMR, Cardiac magnetic resonance; MRI, Magnetic resonance imaging; RWMAs, Regional wall motion abnormalities; ECG, Electrocardiogram.

